**Methods:**

A parallel RCT with a control-experimental, pre- and post-test, repeated-measures design is used in this study. A total of 120 patients will be randomized according to the occurrence of pain. Participants will be recruited face-to-face at the point of care during clinical visits. Participants in the intervention group will receive the Web- and mobile-based The-Optimal-Lymph-Flow intervention and will have access to and learn about the program during the first in-person research visit. Participants in the control group will receive the Web- and mobile-based Arm Precaution program and will have access to and learn about the program during the first in-person research visit. Participants will be encouraged to enhance their learning by accessing the program and following the daily exercises during the study period. Participants will have monthly online self-report of pain and symptoms at 4 and 8 weeks post-intervention. During the two in-person research visits prior to and 12 weeks post-intervention, participants will be measured for limb volume difference, BMI, and complete self-report of pain, symptoms, self-care behaviors, and QOL.

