### Study Population

Study population includes: (1) patients who have been surgically treated for breast cancer more than 3 months (healing usually occurs within 3 months of surgical treatment for cancer); (2) patients who report *persistent or intermittent* pain, including aching, tenderness, soreness; (3) patients may or may not report any of the symptoms related to lymphedema (ie, swelling, heaviness, tightness, firmness, numbness, tingling, stiffness, limb fatigue, limb weakness, and impaired limb mobility of shoulder, arm, elbow, wrist, and fingers); (4) patients may or may not have a history of lymphedema or have been treated for lymphedema; (5) patients have Internet access to the Web- and mobile-based program at home or willing to access the program using the laptop provided by the researchers at the cancer center; (6) ability to understand and the willingness to sign a written informed consent document.

Exclusion criteria are (1) patients who do not report any pain, including aching, tenderness, and soreness; (2) patients who have known metastatic disease or other bulk disease in the thoracic or cervical regions; (3) patients who have lymphedema due to cancer recurrence; (4) patients with documented advanced cardiac or renal disease.

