### Randomization and Blinding

The randomization assignment will be generated by our senior statistician using a computer-generated randomization procedure. Participants will be randomized based on their report of pain/aching/soreness or tenderness to be allocated to intervention and control group. The researchers who perform pre- and post-intervention measurements will be blinded throughout the study to the participants’ assigned arm. Participants will not know which intervention was the intervention of interest and which one was the comparator.

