### Data Collection

#### Data Collection Procedures

Data will be collected at baseline prior to intervention, and at week 12 post-intervention. Data collection at each time point will take approximately 30 minutes. Within one week of enrollment for the clinical trial, patients will have baseline assessment of pain and symptoms, limb volume difference, BMI, and quality of life. The follow-up assessment will occur at week 12 post intervention.

*Two In-Person Research Visits*: (1) prior to intervention there will be baseline assessment of pain and symptoms, limb volume difference, BMI, and quality of life; and (2) 12 weeks post-intervention assessment of pain and symptoms, limb volume difference, BMI, self-care behaviors, and quality of life.

*Two Online Assessments:* patients in the intervention and control group will receive an email that provides a link to assess pain and symptoms as well as quality of life at week 4 and week 8 post-intervention. Confidentiality of the patients will be protected for the online assessment since patients will use their study ID to access the online assessment.

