#### Outcome Measures

*Demographic and Medical Information*: a structured tool is used to gather demographic and medical information and is verified through reviewing participants’ medical records [14,17,19]. The demographic and medical information will be considered as covariates, including expectation of the program, pain medications, age, surgeries, lymph nodes procedure, radiation, chemotherapy, time since surgery, time since lymphedema diagnosis, and hormonal therapy.

*Primary and Secondary Outcome Measures*: primary measure focuses on pain which is assessed during prior to the intervention and week 12 post-intervention in-person visit, as well as week 4 and 8 post-intervention online assessment. Secondary measures include symptoms, limb volume difference by infra-red perometer, BMI, quality of life related to pain. Limb volume difference by infra-red perometer and BMI are only measured prior to and week 12 post-intervention in-person visits. Symptoms and quality of life related to pain are assessed prior to and week 12 post-intervention in-person visit as well as week 4 and 8 post-intervention online assessment.

*Pain and Symptoms Related to Lymphedema:* the Lymphedema and Breast Cancer Symptom Experience Index is a valid and reliable self-report tool to assess pain, including aching, soreness, tenderness, as well as symptoms related to lymphedema (ie, arm swelling, breast swelling, chest wall swelling, heaviness, firmness, tightness, stiffness, burning, stabbing numbness, tenderness, stiffness, redness, blistering, and tingling (pins and needles) [14,17,19]. Each symptom can be treated as categorical variable by choosing a “Yes” or “No” to indicate the presence or absence of a given symptom. Each item can also be rated on a Likert-type scale from 0 (no presence of a given symptom) to 4 (greatest severity of a given symptom). Higher scores indicate more severe symptom presence. A response frame of last three months will be used for all participants to ensure the chronicity of symptom presence during the first in-person visit.

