#### Analysis Plan

We will summarize graphically and numerically the distributions of pain, aching, soreness, tenderness, other symptoms related to lymph fluid accumulation, limb volume differences, BMI, and quality of life as well as covariates (such as medication for pain, age, or education and treatment variable and limb volume and self-care behaviors). The proportion of individuals experiencing pain, aching, soreness, tenderness will be compared between the intervention and control group over time, as will the mean severity ratings and associated quality of life scores. Mean comparisons of number of reported symptoms, limb volume, and BMI will be conducted between the intervention and control group as well as over time.

Bivariate relationships between the variables and treatment group will be assessed using point-biserial correlations and phi coefficients to identify potential covariates for inclusion into statistical models. Linear mixed effects models will be used to analyze continuous outcomes (eg, ratings pain, aching, soreness, tenderness, symptom ratings, and quality of life) and generalized linear mixed models will be used to analyze binary outcomes (presence of pain, aching, soreness, tenderness, and total scores of quality of life). These models will incorporate fixed effects for time, group, and any identified covariates. As indicated by preliminary models to estimate variance effects, models will include random effects for subject-specific slopes and intercepts. A statistically significant fixed effect for group by time interaction will indicate a treatment effect, with the direction of difference determined from mean values. Models will be compared for goodness of fit and modifications to link functions, distributional form, and correlation structure will be made as necessary.

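### For the any-pain composite, eligibility fixes presence at about 100% in both arms at baseline, so the group-by-time interaction is a poor measure of the treatment effect

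*Protocol article*

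**What the plan says.** Study Population requires reported pain (including aching, tenderness or soreness) and excludes "patients who do not report any pain, including aching, tenderness, and soreness". Under Data Collection Procedures, "Within one week of enrollment for the clinical trial, patients will have baseline assessment of pain and symptoms". Under Outcome Measures, "A response frame of last three months will be used for all participants to ensure the chronicity of symptom presence" at the first visit, and each symptom can be scored either yes/no or from 0 to 4.

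The primary endpoint is absence of pain or pain reduction at week 12. In the Analysis Plan, "generalized linear mixed models will be used to analyze binary outcomes (presence of pain, aching, soreness, tenderness" and total quality-of-life scores), with fixed effects for time, group and identified covariates, and random subject intercepts and slopes if indicated. The decision rule is: "A statistically significant fixed effect for group by time interaction will indicate a treatment effect". The section does not say whether baseline is a modelled time, whether time is categorical or linear, or whether presence means any of the four symptoms or each one separately.

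On allocation, the Abstract says "A total of 120 patients will be randomized according to the occurrence of pain", and Randomization and Blinding says "Participants will be randomized based on their report of pain/aching/soreness or tenderness to be allocated to intervention and control group". Neither gives levels.

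**The concern.** A patient must report at least one of the four pain symptoms to enter. Baseline follows within a week and looks back three months, so the composite (any of the four present) should be yes for essentially everyone in both arms. A group-by-time interaction asks whether the arms change differently from a common start. On the logit scale that start is infinite for both arms.

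Absence of pain is one half of the primary endpoint. If the composite is analysed as written, the trial could end with no usable odds ratio for it, or with a test on a term that does not carry the effect. A real difference at week 12 could then be reported as no effect.

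The allocation wording raises a smaller question of the same origin: a yes/no occurrence of pain has only one level among eligible patients, so it cannot balance anything.

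**Working it through.** **The plan's own power figures.** For binary outcomes the plan gives 50 per arm, three repeated observations, r = 0.5, alpha .05 and 80% power. Effective n per arm = 50 × 3 / (1 + 2 × 0.5) = 75. A two-sided two-proportion calculation then gives a detectable odds ratio of 2.59 at a control proportion of 0.5 and 3.46 at 0.1. The plan states 2.6 to 3.5. The control proportions are my assumption, since none is given. For the *t* test, 20% attrition leaves 60 × 0.8 = 48 per arm. The detectable difference at 90% power is 0.67 SD, against 0.7 stated, and power at 0.7 SD is 92.4%. Both statements reproduce.

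**Illustrative data for the composite.** Assumed number with pain out of 48 at weeks 0/4/8/12: control 48/43/41/38, intervention 48/38/34/29.

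*Reading 1: categorical time, baseline included.* The baseline log-odds are ln(48/0) in both arms. In a logistic fit by Newton iteration, the intercept rises by about 1 per iteration (6.2, 11.2, 16.2, 21.2, 26.2 at iterations 5, 10, 15, 20, 25). The standard error of the week-12 interaction goes 4.6, 55, 674, 8,204, 99,949, while the log-likelihood settles at −146.302. In a random-intercept logistic model on simulated data, different starting values reach the same log-likelihood (−131.256) with week-12 interactions from −3.7 to −7.8. The interaction is not identified.

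*Reading 2: linear time, baseline included.* The estimate is finite: interaction −0.27 (SE 0.92), with time scaled to 12 weeks.

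*Reading 3: weeks 4, 8 and 12 only.* The estimates are finite. The week-4 group term is ln(38/10) − ln(43/5) = 1.335 − 2.152 = −0.82 (SE 0.59). The interaction terms are −0.06 (SE 0.79) at week 8 and −0.10 (SE 0.75) at week 12, so nearly all of the effect sits on the group term. The week-12 contrast from the same data is ln(29/19) − ln(38/10) = 0.423 − 1.335 = −0.91, with SE √(1/29 + 1/19 + 1/38 + 1/10) = 0.46. That is an odds ratio of 0.40 (95% CI 0.16 to 0.99).

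*A single symptom.* If one item is present in 40 of 48 at baseline in each arm, the full model gives a finite week-12 interaction of −0.91 (SE 0.72). There is no separation.

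**Power of the named test.** Simulated trials: 48 per arm, everyone positive at baseline, latent correlation 0.7, exchangeable GEE with linear time.

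| Assumed presence at weeks 4, 8, 12 | Interaction, baseline in | Interaction, weeks 4/8/12 only | Week-12 comparison |
|---|---|---|---|
| 80% vs 50% throughout | about 26% | about 5% | about 90% |
| 90/85/80% vs 80/65/50% | about 31% | about 17% | about 88% |

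The week-12 entries can be checked by hand for 80% versus 50%. The pooled SE is √(2 × 0.65 × 0.35 / 48) = 0.0974 and the unpooled SE is √((0.16 + 0.25) / 48) = 0.0924. Then (0.30 − 1.96 × 0.0974) / 0.0924 = 1.18, which gives 88% power. The week-12 group term in the model of weeks 4, 8 and 12 gives 90% to 91%.

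**Allocation.** Set beside the eligibility rule, the Abstract's occurrence of pain is constant. The Methods wording could mean which symptom is reported, and that can vary, but then the two statements differ and no levels are given.

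**The case against.** A reader might infer that the planned model can never give a finite interaction estimate. The document does not support that. Separation needs three choices together: presence means the composite, baseline is a modelled level, and time is categorical. The text leans away from each. It lists the four symptoms individually and scores each one, it counts three repeated observations in the binary power statement, and it speaks of subject-specific slopes. Under linear time, post-baseline times only, or single items below 100%, the estimate is finite. This objection stands and limits the separation to one reading.

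It does not rescue the interaction as the effect measure for the composite, because the two finite readings have low power or put the effect on another term. The plan's allowance for changing link, distribution or correlation structure does not change which term is called the treatment effect. A likelihood-ratio test would survive separation, but without an odds ratio or interval.

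Two further points stand. Severity ratings go through linear mixed models, where separation does not arise, and the plan also compares proportions between arms directly, so the primary endpoint is not lost as a whole.

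On allocation, a reader might infer a failed stratification intended to balance severity. The article never says stratified and never mentions severity in that context, so only unclear wording is established. It also leaves the covariate list open, so omission of a randomisation factor from the models is not established.

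**Conclusion.** The point holds for the composite presence of any pain, aching, soreness or tenderness. Its baseline value is fixed at about 100% by eligibility, and the interaction named as the treatment effect is then either not identified (categorical time with baseline), weak (linear time with baseline, about 26% power against about 90% for a week-12 comparison), or nearly blind to a constant effect (weeks 4, 8 and 12 only, about 5%). This is more than detail left to a fuller document, because the article itself fixes the effect-defining term.

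The 100% follows from the eligibility text, the one-week window and the three-month recall. The power figures rest on assumed presence rates, 48 per arm and a latent correlation of 0.7; the document gives no presence rates. The direction of the result follows from the structure and was the same when the effect emerged gradually. Items below 100% at baseline, the severity models and the reproduced power statements are untouched by the separation. The randomisation wording is a matter for reconciliation only.

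**What to change.** For composite presence of pain, state in the Analysis Plan that the model uses weeks 4, 8 and 12 only, with time as a category. Name the week-12 group contrast as the treatment effect, in line with the stated primary endpoint, and include baseline severity of the four pain items as a covariate. Say explicitly whether presence means any of the four symptoms or each one. Baseline severity is already collected, so this costs only wording, settled before the data are analysed.

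Separately, reconcile the Abstract with Randomization and Blinding: state which factor and levels, if any, were used for allocation, and include that factor in the models. The factor should not be replaced during the trial; nothing in the document shows that this is needed.

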*Limb Volume Difference by Infra-Red Perometer*: perometry 350S will be performed on each arm as it is held horizontally. The perometer maps a 3-dimensional graph of the affected and non-affected extremities using numerous rectilinear light beams, and interfaces with a computer for data analysis and storage. A 3-dimensional limb image will be generated and limb volume will be calculated. This optoelectronic method has a standard deviation of 8.9 ml (arm), less than 0.5% of limb volume with repeated measuring [17,19] .

*Quality of life Related to Pain*: the Pain Impact Questionnaire (PIQ-6), a reliable and valid six question health survey, will be used to measure pain severity and the impact of pain on an individual's functional health and well-being. The PIQ-6 measures the severity of pain and its impact on work and leisure activities, as well as on emotional well-being within a variety of diseases and general populations. High PIQ-6 *T* scores indicate greater pain impact/worse health [21-23].

*Height, Body Weight, and BMI*: height will be measured to the nearest 0.1 cm with a portable stadiometer (Scale-Tronix 5002 Stand on Scale, Scale-Tronix Company, Carol Stream, IL, USA) without shoes [25]. An electrical device (InBody 520, Biospace Co, Ltd, Seoul, Korea) will be used to measure the participants’ body weight, BMI is calculated using the formula: weight (kg)/height (m^2^) [25].

*Practice of Self-Care Behaviors:* Risk Reduction Behavior Checklist is a structured self-report checklist that will be used to quantitatively and qualitatively assess patients’ practice of self-care behaviors at the study endpoint of 12-week after intervention [17,19]. The checklist include a list of self-care behaviors that promote lymph flow, eg, muscle-tightening deep breathing, muscle-tightening pumping, shoulder exercises, large muscle exercises, and having nutrition-balance and portion-appropriate diet, adequate hydration and sleep, as well as compression therapy for lymphedema.

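### The Analysis Plan puts quality of life in both the linear and the binary model family, with no cut-off; the between-arm use of baseline for symptom count, limb volume and BMI could also be fixed at no cost

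*Protocol article*

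**What the plan says.** **Quality of life.** One sentence of the Analysis Plan contains both assignments. Its first half reads "Linear mixed effects models will be used to analyze continuous outcomes (eg, ratings pain, aching, soreness, tenderness, symptom ratings, and quality of life". Its second half assigns to generalized linear mixed models the "binary outcomes (presence of pain, aching, soreness, tenderness, and total scores of quality of life". Outcome Measures describes the instrument, the PIQ-6, as scored on a T scale: "High PIQ-6 *T* scores indicate greater pain impact/worse health". The article gives no threshold that would turn this score into a yes/no outcome. Objectives and Hypotheses includes pain-related quality of life in the primary objective, while Outcome Measures lists it as secondary.

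**Number of symptoms, limb volume and BMI.** The Analysis Plan states: "Mean comparisons of number of reported symptoms, limb volume, and BMI will be conducted between the intervention and control group as well as over time". The following paragraph, on mixed models, does not name these three. On timing, Outcome Measures says: "Limb volume difference by infra-red perometer and BMI are only measured prior to and week 12 post-intervention in-person visits". For the mixed models the effect criterion is: "A statistically significant fixed effect for group by time interaction will indicate a treatment effect". Covariates enter the models after a screen of their correlation with treatment group.

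**The concern.** A T score is a numerical scale. A model for a binary outcome can take it only after it has been dichotomised, and the article gives no rule for that. Two analysts following the plan could therefore produce different quality-of-life results, one a mean difference and the other an odds ratio at a threshold of their own choosing. The same section also allows link function and distributional form to be modified as necessary, so the text does not settle the choice. The outcome is not peripheral, because it appears in the primary objective.

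The second matter is one of precision. For symptom count, limb volume difference and BMI, the only analysis named is a comparison of means, and the text does not say whether the between-arm test uses the baseline value. The covariate screen does not ensure it either: correlation with treatment group picks up chance imbalance between arms, not the ability to predict the outcome. If week-12 means alone were compared, information already collected at baseline would go unused.

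**Working it through.** **1. Quality of life: the statements side by side**

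| Place | Treatment of quality of life |
|---|---|
| Outcome Measures | PIQ-6 T score, higher is worse; no cut-off |
| Analysis Plan, first paragraph | scores, mentioned alongside mean severity ratings |
| Analysis Plan, second paragraph, first half of the model sentence | continuous, linear mixed model |
| Analysis Plan, second paragraph, second half of the same sentence | total score binary, generalized linear mixed model |

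Three of the four fit a continuous score. The fourth conflicts with them and cannot be carried out without a threshold that the article does not contain. No arithmetic applies.

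**2. Symptom count, limb volume difference and BMI: what baseline is worth**

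Inputs from Sample Size and Power Calculations: 60 per arm, 20% attrition, two-sided alpha 0.05, and r = 0.5 between observations (stated there for the mixed models). The analysable number is 60 × 0.8 = 48 per arm. The baseline-to-week-12 correlation for these outcomes is not given, so r = 0.8 to 0.95 is an assumption.

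The plan's own figure first. A two-sample t test with 48 per arm and 90% power detects 0.669 SD, which rounds to the stated 0.7 SD. That figure reproduces and is not in question.

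At 80% power the same test detects 0.578 SD. The detectable difference scales with the SD of the quantity analysed, in units of the week-12 SD and assuming equal SDs at both visits:

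- week-12 value alone: 0.578
- change from baseline: 0.578 × √(2(1 − r))
- baseline-adjusted (ANCOVA): 0.578 × √(1 − r²)

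| r | Week 12 alone | Change | Baseline-adjusted |
|---|---|---|---|
| 0.5 | 0.58 | 0.58 | 0.50 |
| 0.8 | 0.58 | 0.37 | 0.35 |
| 0.9 | 0.58 | 0.26 | 0.25 |
| 0.95 | 0.58 | 0.18 | 0.18 |

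The patient numbers needed for equal power, change analysis relative to ANCOVA, stand in the ratio 2(1 − r)/(1 − r²) = 2/(1 + r). This is 1.33 at r = 0.5, 1.11 at 0.8 and 1.05 at 0.9.

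So adjustment gains a good deal over a week-12-only comparison when r is high, but little over a change analysis. With two visits, a group-by-time interaction is a comparison of change between the arms.

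**The case against.** The quality-of-life wording may be no more than a misplaced phrase, since every other mention treats the outcome as a score and nothing in the article says that it will be dichotomised. That is probably how it arose. The sentence still gives two incompatible instructions and should be corrected.

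The objection carries more weight for the other three outcomes. A reader might infer that limb volume and BMI are to be compared as raw means with baseline left out. The text does not say so. It plans comparisons over time as well as between groups, and with only baseline and week 12 available, a comparison over time must use baseline. The sentence sits in a largely descriptive paragraph, and the list of outcomes for the linear mixed model is open, introduced as examples, so these outcomes may be modelled too. Nor does the article plan within-arm tests as evidence of effect. Random slopes, which two visits could not support together with random intercepts and residual error, are conditional on preliminary models, so a random intercept alone is permitted.

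A condensed article may also leave baseline handling to the full analysis plan, and an unadjusted comparison in a randomised trial is valid, only less precise. Limb volume is analysed as a difference between limbs, which may already remove some variation between women, so a high r should not be taken for granted there. All of this stands, and it makes the second part a suggestion and not the correction of an error.

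**Conclusion.** The contradiction on quality of life is established from the text alone. The total score is listed as binary, the instrument gives a T score, no cut-off exists, and the same sentence assigns quality of life to the linear model. It should be corrected because it concerns an outcome named in the primary objective.

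For symptom count, limb volume difference and BMI, the supported statement is narrower: the article does not secure the use of baseline in the between-arm test. Against a week-12-only comparison, adjustment lowers the detectable difference from about 0.58 SD to 0.50 SD at the document's r = 0.5, and to 0.35 to 0.25 SD at an assumed r of 0.8 to 0.9. Against a change analysis, the gain at those high correlations is about 0.01 to 0.02 SD. These figures assume 48 per arm, equal SDs at the two visits and a linear relation to baseline.

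It would go too far to conclude that the continuous secondary outcomes as a group get the wrong analysis, because symptom ratings are assigned to a linear mixed model. Nor do the documents support a prediction that the limb volume and BMI comparisons would almost certainly be null: they give neither an expected effect nor a correlation for these outcomes.

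**What to change.** 1. In the Analysis Plan, delete the total quality-of-life score from the list of binary outcomes. State that the PIQ-6 T score is analysed only in the linear mixed model, using its baseline value.
2. As an improvement, for number of symptoms, limb volume difference and BMI, name the between-arm difference at week 12 adjusted for the baseline value as the analysis. For limb volume difference and BMI, which have two visits, this is an ANCOVA. Include the baseline value by specification, whatever the covariate screen shows.

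Both are changes of wording. Baseline values of these outcomes are already collected, so no extra visits, measurements or patients are needed.

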#### Sample Size and Power Calculations

We will enroll a total of 120 participants: 60 participants in The-Optimal-Lymph-Flow intervention and 60 participants in the Arm Precaution control group to account for a potential attrition of 20%, which has been observed in the prior studies in breast cancer survivors [10]. This will yield an adequate analytic sample size. Even with 20% attrition based on a 2 sample 2-sided *t* test with alpha=.05 and power of 90%, we can detect a difference of 0.7 standard deviations in the difference between the presence of pain in the intervention group compared to the control group at 8 weeks or at 12 weeks. The projected sample size will also provide sufficient statistical power for mixed regression models. For linear mixed models of continuous outcomes (eg, pain ratings), statistical power will exceed 80% to detect a medium effect, assuming a constant group effect, correlations of r=.5 between observations, alpha=.05, and compound symmetry of the covariance structure.

For binary outcomes, based on the three repeated observations with a conservative estimate for the assumed correlation of r=0.5 between observations, alpha=.05, sample size of n=50 per treatment arm will have power of 80% to detect odds ratios of the difference between groups ranging from 2.6 to 3.5 (small to medium effects).

Adequacy of sample size will be monitored during the analyses in three ways: (1) assessing sufficiency to estimate the number of model parameters identified by preliminary analyses; (2) examining model fit indices (eg, intra-class correlation coefficient to assess fit of random effects) to ensure data adequately support models generated, and (3) assessing the adequacy to accurately estimate model parameters by generating confidence intervals.

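### Baseline scores are collected but not prespecified as covariates, and covariates are screened on association with treatment group; at the plan's r=.5 a continuous week-12 contrast has relative variance 1.00 instead of 0.75

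*Protocol article*

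**What the plan says.** Under Outcome Measures, the "primary measure focuses on pain which is assessed during prior to the intervention and week 12 post-intervention in-person visit", with online assessments at weeks 4 and 8. Symptoms and PIQ-6 follow the same four-point schedule. Each symptom item can be scored as present or absent, or rated from 0 to 4.

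The same section states that the demographic and medical information "will be considered as covariates, including expectation of the program, pain medications, age, surgeries, lymph nodes procedure, radiation, chemotherapy", followed by time since surgery, time since lymphedema diagnosis and hormonal therapy. The Analysis Plan adds examples such as education, limb volume and self-care behaviours. No baseline pain, symptom or PIQ-6 score appears in either place.

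The Analysis Plan identifies potential covariates by point-biserial correlations and phi coefficients with treatment group, and gives no threshold. It then sets the model: "These models will incorporate fixed effects for time, group, and any identified covariates". The test is set as well: "A statistically significant fixed effect for group by time interaction will indicate a treatment effect". It does not say whether the baseline score is a row of the outcome vector or whether the arms share a baseline mean.

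The mixed-model power statement for continuous outcomes is made "assuming a constant group effect, correlations of r=.5 between observations, alpha=.05, and compound symmetry of the covariance structure".

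**The concern.** In a randomised trial, association between a baseline variable and treatment group arises by chance. A screen on that association takes no account of whether the variable predicts the outcome. A woman's own baseline rating is probably among the strongest predictors of her week-12 rating. If randomisation balances it well, the screen leaves it out. The screen also makes the final model depend on the baseline data observed.

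Fitting a mixed model does not in itself recover the lost information. If baseline is an outcome row and the model has a free group effect plus group by time, the week-12 interaction contrast is a comparison of changes from baseline. If only the follow-ups are modelled, baseline is not used at all. Either way, precision is given up in a small trial on data that are already collected.

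**Working it through.** **Inputs**
- Allocation: "60 participants in The-Optimal-Lymph-Flow intervention and 60 participants in the Arm Precaution control group". With the stated 20% attrition, 60 × 0.8 = 48 per arm.
- Two-sided t test: a "test with alpha=.05 and power of 90"%, for which "we can detect a difference of 0.7 standard deviations".
- Correlation r=.5 with compound symmetry, from the mixed-model power statement.
- The article puts no number on a medium effect. I assume 0.5 SD.

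Power below is from the two-sided noncentral t distribution unless noted.

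**The plan's own figures**
- t test: 48 per arm detects 0.669 SD at 90% power, which rounds to 0.7. Power at exactly 0.7 SD is 92.4%.
- Mixed model with a constant group effect: the mean of three observations has relative variance (1 + 2r)/3 = (1 + 1)/3 = 0.667. Power at 0.5 SD is 84.4% (85.1% by the normal approximation). The claim of more than 80% reproduces without any baseline adjustment.

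**Variance of the week-12 contrast, relative to SD²**
- Baseline as an outcome row, free group difference: 2(1 − r) = 2 × 0.5 = 1.00.
- Follow-ups only: 1.00.
- Adjusted for the same measure at baseline: 1 − r² = 1 − 0.25 = 0.75.

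Generalised least squares over four visits under compound symmetry gives the same values: 1.00 for the saturated group-by-time model and 0.75 with a common baseline mean. If time is instead fitted as a linear trend, the values are 0.90 and 0.66, so a loss remains.

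The adjusted variance is never the larger one: 1 − (1 − r²) = r² ≥ 0, and 2(1 − r) − (1 − r²) = (1 − r)² ≥ 0.

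**Power at week 12, 48 per arm, r=.5**

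| True difference | Unadjusted (either reading) | Adjusted | Gain |
|---|---|---|---|
| 0.5 SD (assumed) | 67.9% | 79.9% | 12.0 points |
| 0.7 SD (plan) | 92.4% | 97.5% | 5.1 points |

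The difference detectable at 90% power falls from 0.669 SD to 0.669 × √0.75 = 0.579 SD. For the effect averaged over the three follow-ups, the variance falls from 0.667 to 0.667 − 0.25 = 0.417, and power at 0.5 SD rises from 84.4% to 96.4%.

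**Dependence on r (week 12, 0.5 SD)**

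| r | Change contrast | Follow-up only | Adjusted |
|---|---|---|---|
| .3 | 54% | 68% | 72% |
| .5 | 68% | 68% | 80% |
| .6 | 77% | 68% | 86% |
| .7 | 88% | 68% | 92% |

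Against the change contrast the gain shrinks as r rises, from 18 points at r=.3 to 5 at r=.7. Against follow-up only it grows, from 4 points to 25.

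**The case against.** The strongest reply is that group by time with baseline as an outcome row is a standard and unbiased analysis in a randomised trial. The design is described as pre- and post-test, so baseline is probably in the model already, and the handling of baseline means is detail that an article may leave to a fuller plan. This stands in part. The issue is efficiency, not validity. But the article does state a covariate rule, and that rule uses the wrong criterion. A free baseline difference also recovers only change-score precision.

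Four stronger readings are tempting, and the document does not support them.

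- **The trial is underpowered.** A reader might set 68% against the claim of more than 80%. That claim is for a constant group effect over repeated observations and reproduces at about 84%. The article's only numeric effect size for week 12 is 0.7 SD, where unadjusted power already exceeds 90%.
- **Baseline scores are barred.** Both covariate lists are open-ended, and a chance imbalance could admit a baseline score. If a 5% threshold is assumed (none is stated), that would happen about one time in twenty for each score.
- **The figures describe the whole primary endpoint.** That endpoint is absence of pain or pain reduction. Eligibility requires some pain, so presence of pain is essentially constant at baseline, and 1 − r² does not carry over to a binary outcome.
- **Enrolling women because they have pain biases the change contrast through regression to the mean.** That selection acts on both arms alike. Only a chance imbalance at baseline matters.

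It is also fair to say that r=.5 may not describe the baseline to week-12 correlation. The binary-outcome power paragraph counts three repeated observations against four scheduled assessments, and the three-month recall frame is stated only for the first visit. Nor does r=.5 say anything about PIQ-6 as a covariate for pain.

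**Conclusion.** The concern holds as a matter of efficiency and covariate selection. The association-with-group screen is a poor rule in a randomised trial, and baseline pain, symptom and PIQ-6 scores should not depend on it. For continuous ratings at r=.5 under compound symmetry, adjustment cuts the week-12 variance by 25% under either reading with visits as categories. With 48 per arm this is about 12 points of power if the true difference is 0.5 SD, which is my assumption, and about 5 points at the plan's 0.7 SD. The gain varies with r as tabulated. No stated power figure fails, and the article gives no basis for a figure on absence of pain. The change is worth making, but the trial does not depend on it.

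**What to change.** In the Analysis Plan, prespecify for each continuous outcome (pain, aching, soreness and tenderness ratings, other symptom ratings, PIQ-6) that the woman's own baseline value of that measure is a fixed covariate, with the follow-up visits as outcomes. Equivalently, keep baseline as an outcome and give both arms a common baseline mean. State which of the two is used. Enter baseline pain severity in the generalized linear mixed model for presence of pain. Include these terms whatever their association with treatment group.

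The cost is a few sentences and a few degrees of freedom. The values are already collected, so no extra women, visits or measurements are needed.
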